## Abstract

**Background:**

The high incidence of falls associated with Parkinson’s disease (PD) increases the risk of injuries and immobility and compromises quality of life. Although falls education and strengthening programs have shown some benefit in healthy older people, the ability of physical therapy interventions in home settings to reduce falls and improve mobility in people with Parkinson’s has not been convincingly demonstrated.

**Methods/design:**

180 community living people with PD will be randomly allocated to receive either a home-based integrated rehabilitation program (progressive resistance strength training, movement strategy training and falls education) or a home-based life skills program (control intervention). Both programs comprise one hour of treatment and one hour of structured homework per week over six weeks of home therapy. Blinded assessments occurring before therapy commences, the week after completion of therapy and 12 months following intervention will establish both the immediate and long-term benefits of home-based rehabilitation. The number of falls, number of repeat falls, falls rate and time to first fall will be the primary measures used to quantify outcome. The economic costs associated with injurious falls, and the costs of running the integrated rehabilitation program from a health system perspective will be established. The effects of intervention on motor and global disability and on quality of life will also be examined.

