### Power calculation and sample size

The primary dependent variable of falls frequency over 12 months was used to determine sample size. Based on previous studies [8,52] and setting power at 80%, alpha at 5% and with a drop-out rate of 20%, a sample size of 90 is required in each group to detect a clinically significant difference of 25% reduction in falls frequency in the intervention group. This sample size will also be sufficient to identify between-group differences in the secondary outcomes of the Movement Disorders Society – Unified Parkinson’s Disease Rating Scale (MDS-UPDRS) [53] and Parkinson’s Disease Questionnaire-39 items (PDQ-39) [54,55].

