### Outcome measures

#### Primary

The primary outcome measure will be falls, defined as “an unexpected event in which the participants comes to rest on the ground, floor or lower level” [59]. Falls will be monitored during the 6 weeks intervention and for 12 months thereafter, consistent with the recommendations of the ProFaNE consensus group . Participants will mark all falls on the day they occur on a falls calendar, [60]or mark a month without falls by ticking a box marked “I had no falls”. Pre-paid envelopes will be provided for the return of each month’s calendar sheet. Injurious falls, defined as a fall requiring medical attention or any healthcare utilization, will be marked with a yellow sticker. Telephone calls will be used to remind participants who have not returned their monthly sheet. Calls will also investigate each injurious fall using a set questionnaire that examines the health and economic sequelae of the fall based on data from Medicare Australia, self-reported health care utilization and out-of-pocket expenditure.

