### Statistical analysis

#### Primary

Falls, as the primary variable of interest, will be examined in four ways consistent with the recommendations of the ProFaNe group [60]:

i. number of fallers

ii. number of multiple fallers (two or more falls)

iii. falls rate and time to first fall

iv. relative risk (RR) will be calculated to compare number of fallers and number of multiple fallers between the two groups.

The number of falls and the falls rate per person per year in the two groups will then be compared using negative binomial regression models, an approach that takes into account all falls and adjusts for varying duration of follow up. Injurious falls, as defined above, will be analyzed in the same way.

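### The primary falls outcome is defined differently in the abstract, sample-size, outcome, economic and analysis sections, so the measure that decides the falls claim is not fixed

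*Protocol article*

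**What the plan says.** The article describes the primary outcome in several places.

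- **Abstract, Methods/design:** "The number of falls, number of repeat falls, falls rate and time to first fall will be the primary measures used to quantify outcome". Four measures, plural and unranked.
- **Background, primary aim:** falls incidence over 12 months.
- **Power calculation and sample size:** "The primary dependent variable of falls frequency over 12 months was used to determine sample size". One variable, with 80% power, one alpha of 5%, 20% drop-out, 90 per group and a 25% reduction.
- **Outcome measures, Primary:** "The primary outcome measure will be falls, defined as" a type of event. No summary measure is chosen.
- **Economic evaluation:** the cost-effectiveness ratio tied to the primary outcome is cost per fall prevented, which again implies one outcome.
- **Statistical analysis, Primary:** "Falls, as the primary variable of interest, will be examined in four ways consistent with the recommendations of the ProFaNe group". The four items are number of fallers; number of multiple fallers; falls rate together with time to first fall; and a relative risk. On the last, "relative risk (RR) will be calculated to compare number of fallers and number of multiple fallers between the two groups". The next sentence adds: "The number of falls and the falls rate per person per year in the two groups will then be compared using negative binomial regression models".

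**The concern.** A reader who wants to know whether the integrated program reduced falls needs one measure, named in advance, that decides it. The sample-size paragraph and the economic evaluation suggest a count or rate of falls. The abstract and the analysis section give several measures equal standing and do not list the same ones.

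The measures can disagree. The Background describes an earlier six-week home-program trial in which falls showed only a trend while repeated falls fell significantly. With that pattern here, a reader of the abstract could call the trial positive and a reader of the sample-size paragraph could not. The choice of section could then be made after the results are known, and the 5% error rate used for planning would no longer describe the falls claim.

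**Working it through.** **1. The definitions side by side.**

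| Place | Primary measure(s) |
|---|---|
| Abstract | number of falls; number of repeat falls; falls rate; time to first fall |
| Background, aim | falls incidence over 12 months |
| Sample size | falls frequency over 12 months |
| Outcome measures | falls, no summary measure |
| Economic evaluation | cost per fall prevented |
| Statistical analysis | fallers; multiple fallers; falls rate; time to first fall; then number of falls |

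Number of falls, falls rate and time to first fall appear in both the abstract and the analysis section. Number of fallers appears only in the analysis section. Repeat falls (events) in the abstract become multiple fallers (persons) in the analysis. The fourth way in the analysis list, relative risk, is a statistic and not an outcome. Neither list is ranked.

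**2. Does the planned 90 per group show which measure was meant?** It does not. For a rate ratio of 0.75, the negative binomial formula is

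n per group = (1.960 + 0.842)² × (1/μ₁ + 1/μ₂ + 2k) / (ln 0.75)².

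The control mean μ₁ and the dispersion k are not given. Over assumed means of 1 to 20 and k of 0 to 3, n runs from 12 to 791 before drop-out. Read instead as proportions of fallers, 60% against 35% (two-sided, continuity-corrected) gives 70, and 70/0.8 = 87.5, so 88. A relative reduction from 60% to 45% (two-sided, uncorrected) gives 173, and 173/0.8 = 216.25, so 217. The stated 90 cannot be reproduced for the falls rate, and the near match at 88 does not show what was done.

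**3. False-positive risk if several measures could each carry the claim.** Inputs from the article are 90 per group, 20% drop-out (90 × 0.8 = 72 evaluable), alpha 5%, over 60% falling per year, and more than half of those falling more than once. The following are assumptions:

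- each measure is tested at two-sided 5%;
- any one positive result counts as success;
- time to first fall is tested by log-rank, since no test is named;
- follow-up is one year for everyone;
- falls follow a gamma-Poisson process, which induces the correlation between the measures.

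Fallers and multiple fallers were compared by chi-square and the falls rate by a negative binomial likelihood-ratio test. There were 10,000 null trials per row, with a Monte Carlo standard error of about 0.3 points.

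| Fallers / multiple fallers | Mean, k | Any of four | Any of three* | Rate only |
|---|---|---|---|---|
| 60% / 30% | 1.14, 0.45 | 12.0% | 10.9% | 5.2% |
| 60% / 35% | 1.42, 0.90 | 12.3% | 11.1% | 5.7% |
| 60% / 45% | 3.26, 2.36 | 12.3% | 11.4% | 5.3% |
| 68% / 50% | 2.87, 1.43 | 13.0% | 11.7% | 5.4% |

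*Closest to the abstract's list: number and rate of falls count as one model, and multiple fallers stand in for repeat falls.

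Smaller runs of 3,000 trials at 72 and 90 per group, including 50% fallers, gave 10.8% to 12.8% for any of four.

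**4. Cross-check on correlation.** Four independent tests would give 1 − 0.95⁴ = 18.5%. Four equally correlated normal test statistics give 14.4% at a correlation of 0.6, 13.1% at 0.7, 11.4% at 0.8 and 9.3% at 0.9. The simulated 12% to 13% corresponds to strongly correlated measures, as expected when all come from the same falls record.

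**The case against.** The best defence is that the article does point to one primary outcome. The sample-size paragraph uses the singular with one alpha, the primary aim is falls incidence, the economic ratio is per fall prevented, and the negative binomial comparison of falls and falls rate is already planned. The several summaries are presented as following ProFaNE recommendations, and reporting them is good practice. An abstract is condensed, and repeat falls and multiple fallers are close in meaning. Testing order and alpha allocation commonly sit in an analysis plan that is not shown.

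Much of this stands. It would be wrong to say that nothing in the article points to a leading measure, and the absence of a multiplicity rule is not itself a fault here.

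A reader might also infer that the plan tests four co-primary outcomes at 5% each and so has a 12% error rate. The article does not support that. Its 5% appears only in the sample-size paragraph, for one variable. The relative risks may be meant as estimates only, no test is named for time to first fall, and no success rule of any one positive is stated. Nor is 18.5% a fair figure, because it treats strongly related measures as independent.

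The defence does not remove the printed disagreement. The abstract expressly calls four measures primary, the analysis section puts a different set under the primary heading, and neither gives way to the sample-size variable. An analysis plan could add a testing rule, but these sections would still contradict each other.

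**Conclusion.** The point holds as an inconsistency in the definition of the primary outcome. Falls frequency in the sample-size paragraph is the nearest to a single primary measure, but the abstract and the analysis section do not treat it as such, so the measure that decides the falls claim is not fixed.

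The size is conditional. If every measure were tested at two-sided 5% and any one positive were taken as success, the false-positive risk would be about 11% to 13%. With the falls rate alone named in advance it was 5.2% to 5.7% in the same simulations, which is the nominal 5% plus a slight small-sample excess of the likelihood-ratio test. The range rests on the assumptions listed with the simulation. It shows what is at stake if the ambiguity stays and is not the error rate of the plan as written.

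**What to change.** Name one primary outcome and one test: the falls rate ratio (integrated rehabilitation over life skills) over the stated follow-up, from the negative binomial model already planned, adjusted for each participant's follow-up time, at two-sided 5%. This fits the sample-size variable and the cost per fall prevented. State the follow-up period in the same words throughout, since monitoring covers the six intervention weeks plus 12 months while the sample size refers to 12 months.

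Make number of fallers, multiple fallers (repeat falls) and time to first fall secondary. Report them with confidence intervals and no confirmatory claim, or test them in a fixed sequence after the primary. Use the same wording in the abstract, the sample-size paragraph, the outcome section and the analysis section, and do not count relative risk as an outcome.

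The cost is wording, and the other measures lose primary status. Data collection and the planned number do not change, although this does not confirm that 90 per group suffices for the rate ratio.

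Keeping four primaries with a Bonferroni split would cost more. Each would be tested at 0.05/4 = 0.0125 (z = 2.498). A test with 80% power at 5% would then have Φ(1.960 + 0.842 − 2.498) = Φ(0.304) ≈ 62% power, or would need (2.498 + 0.842)² / (1.960 + 0.842)² ≈ 1.42 times the sample size.

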**Discussion:**

This study will provide new evidence on the outcomes and cost effectiveness of home-based movement rehabilitation programs for people living with PD.

**Trial registration:**

The trial is registered on the Australian and New Zealand Clinical Trials Registry (ACTRN12608000390381).

## Background

Most people with idiopathic Parkinson’s disease (PD) live at home or in the community. A major aim of physical therapy is to enable them to remain at home safely for as long as possible [1-3]. Even though it is estimated that more than 7 million people worldwide have PD [4], there have been few investigations of the most effective home-based exercise and rehabilitation programs for those with this debilitating condition. Falls occur often in people with idiopathic PD as the disease progresses [5,6], with fall rates of over 60% per annum reported [7,8]. More than half of these individuals fall more than once every year [8-10]. It appears likely that the cognitive difficulties frequently associated with PD aggravate the risk of falling, particularly by impairing attention [11].

Potential injury is not the only adverse consequence of a fall. Falling may lead to a fear of falling [12,13], which can in turn result in further falls [14,15]. In people with PD, fear of falling has been associated with an increased risk of frequent falls [16]. Falls often lead a person to reduce their activity levels [14,17,18], community ambulation [19] and their participation in outdoor activities [20], leading to loss of fitness and independence.

Falls not only compromise quality of life [21], but can sometimes impact negatively on caregiver quality of life, with reported issues including depression, sustained productivity losses, fear for their spouse, and injuries sustained in trying to prevent their spouse’s fall [22,23]. The costs from health care service utilization following falls are also substantial [24]. A recent study [25] found annual direct costs of medical care in the USA to be $US23,101 per person in people with PD and only $US11,247 in matched controls, noting that falls were substantial contributors to the difference.

There are several approaches to physical therapy that can be delivered within the home. One effective method, known as movement strategy training (MST), teaches the individual to compensate for the disabling movement disorders that occur in PD. Based on studies by Morris and Iansek [2,26,27], these strategies teach people to use attentional strategies to consciously bypass the basal ganglia, instead using the frontal cortex to initiate and execute functional activities. Motor performance is enhanced by the use of structured practice, which breaks down complex movement sequences into segments and focuses attention on each segment before practicing the activity as a whole. Additional components of MST are the mental rehearsal of forthcoming movements, conscious focus on the movement as it occurs, and the use of supplementary visual or auditory cues. While MST can improve the ability to move [28], its ability to prevent falls within the home and community has not yet been confirmed.

Progressive resistance strength training (PRST) is an exercise therapy that can increase the ability of muscles to generate force. Strength is reduced in many people with PD [29,30] most likely because hypokinesia and aging lead to reduced physical activity and disuse. There is preliminary evidence that PRST for people with Parkinson’s can result in increased muscle strength and hypertrophy [31], improved walking ability [30] and enhanced balance [32,33]. Although PRST has been shown to reduce falls in people with musculoskeletal conditions such as osteoporosis [34], it remains to be seen whether PRST can minimize falls and reduce injuries in people with PD who live at home.

Education packages about the causes and prevention of falls have successfully reduced falls incidence in older people without PD, both in acute and sub-acute care [35] and as part of a multi factorial intervention in community dwelling older people [36-38]. Because PD is more prevalent in the aged population, people with this chronic condition are likely to experience many of the same risk factors for falls as their contemporaries, suggesting that such education packages may also be effective. A study of PD by Sadowski et al. [39] found they had little knowledge of the risk factors specific to PD, despite having fallen. Falls prevention programs are arguably cost-effective [40,41], warranting their evaluation in PD.

Preliminary evidence suggests that an integrated program of progressive resistance strength training, movement strategy training, physical activities, and falls education may reduce falls and disability and improve quality of life in those with PD [7,42,43]. Although these interventions have been investigated independently in the PD literature [44-46], the effects of combining them to provide an optimal package remain unclear. A recent report of an integrated program of group strength and balance exercises in 130 community dwelling people with PD did not identify a significant reduction in fall rates [43]; however, there were differences in the incidence rate ratio (IRR) of falls that may have been clinically meaningful (IRR 0.68 during intervention; 0.74 during follow-up). While the intervention utilized exercises previously prescribed for the frail elderly or older recurrent fallers, there was no focus on the specific difficulties encountered in PD, such as turning or gait initiation problems, and no falls education was provided.

Another randomized controlled trial of integrated therapy examined the effect of a 6 weeks home program on falls rate in a sample of 142 community-dwelling individuals with PD who reported falling in the previous year [7]. The intervention of strengthening, flexibility, balance and gait exercises incorporated strategies on falls prevention and for gait initiation and compensation, but no specific falls education program. Despite the addition of some PD-specific activities, there was only a trend to fewer falls and injurious falls in the exercise group, although near falls and repeated falls were significantly decreased in that group.

Most previous trials of exercise therapy in PD have evaluated rehabilitation in the hospital [28] or outpatient clinic setting [47,48]. Therapy provided in the home, such as by Ashburn et al. [7], rather than the clinic may be more appropriate for a relatively frail, generally elderly population as it is convenient, accessible and affordable. Obviating the need for travel may reduce stress on people with PD and the significant others in their lives. Home-based therapy may also allow for treatment of more disabled people, who would have difficulty travelling to a clinic. A less obvious benefit is the specificity of home training. Movement strategy training focuses on improving an individual’s movement difficulties, such as freezing when turning the corner into the bathroom. While practice in a clinical setting may aim to replicate the turn in direction and angle during treatment, only on-site training can be fully specific. There is some evidence that PD reduces the flexibility of motor learning, increasing the need for task-specific practice [49]; thus home-based therapy seems particularly suitable for people with this condition.

The primary aim of the current study is to investigate whether a short (6 weeks) integrated home rehabilitation program (IR) comprising progressive resistance strength training, movement strategy training and falls prevention education reduces falls incidence over 12 months when compared to a home-based control “life skills” group. Secondary aims are to examine the effects of the IR program on disability and quality of life relative to the control group, and to explore the outcome of injurious falls. An economic evaluation from the perspective of the health care system will be carried out alongside the clinical trial.

## Methods/design

### Design

This study will be a prospective controlled trial with random allocation stratified by recruitment source to control for possible bias. Intention to treat analysis will be used and assessors blinded to group allocation. A concurrent economic analysis will evaluate the costs of falls and their management, as well as the costs of implementing the therapy intervention.

### Participants

Community-dwelling people with PD from metropolitan Melbourne will be recruited via hospital-based neurologists and the state Parkinson’s support group if they have a neurologist-confirmed diagnosis of idiopathic PD. Other inclusion criteria are: aged above 21 years; Hoehn and Yahr [50] of < 5, denoting the ability to walk independently with or without an aid; no overt dementia as determined by a Mini-Mental State Examination [51] score of >23/30, age adjusted. Participants must be able to follow simple instructions delivered in English, provide written consent to participation in the study and be medically safe to undertake an exercise program as determined by their neurologist.

### Power calculation and sample size

The primary dependent variable of falls frequency over 12 months was used to determine sample size. Based on previous studies [8,52] and setting power at 80%, alpha at 5% and with a drop-out rate of 20%, a sample size of 90 is required in each group to detect a clinically significant difference of 25% reduction in falls frequency in the intervention group. This sample size will also be sufficient to identify between-group differences in the secondary outcomes of the Movement Disorders Society – Unified Parkinson’s Disease Rating Scale (MDS-UPDRS) [53] and Parkinson’s Disease Questionnaire-39 items (PDQ-39) [54,55].

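### The stated 80% power for a 25% reduction in falls frequency with 90 per group does not hold if the reduction is relative and tested by the planned negative binomial regression

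*Protocol article*

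**What the plan says.** Under Power calculation and sample size, the article sizes the trial on falls frequency over 12 months, "setting power at 80%, alpha at 5% and with a drop-out rate of 20" percent. It concludes that "a sample size of 90 is required in each group to detect a clinically significant difference of 25% reduction in falls frequency". It refers to two earlier studies for the inputs and prints neither a control-group value nor a dispersion, a test or the sidedness.

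Under Statistical analysis, Primary, the number of falls and the falls rate are "compared using negative binomial regression models", with allowance for differing follow-up. The numbers of fallers and of multiple fallers are compared by relative risk.

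The only fall figures in the document that bear on a baseline are in the Background: "with fall rates of over 60% per annum reported" and "More than half of these individuals fall more than once every year". The first is a percentage of people who fall, although it is called a rate.

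**The concern.** Sample size, power, alpha, drop-out and effect are all stated, so they can be checked against each other and against the planned model. Fall counts vary widely between people, and a rate ratio of 0.75 is a modest effect for such data. Seventy-two to 90 per group looked far too few.

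The section itself calls a 25% reduction clinically significant. If the trial is described as having 80% power for it but is more likely than not to miss it, a non-significant result would be misread as showing that the programme does not prevent a worthwhile share of falls. The cost per fall prevented rests on the same between-group difference.

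**Working it through.** **Inputs.** From the sample-size section: 90 per group, 90 × 0.8 = 72 after drop-out, power 80%, alpha 5% (two-sided assumed), 25% reduction. Assumed from the Background: 60% or more fall in a year, and at least half of fallers fall again. The second is read as P(2 or more falls | at least 1 fall) ≥ 0.50.

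**1. Reproducing 90 from proportions of fallers.**
n per group = [1.96√(2p̄(1−p̄)) + 0.8416√(p₁(1−p₁) + p₂(1−p₂))]² / (p₁−p₂)².

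- Relative 25%, 60% to 45%: (1.384 + 0.588)² / 0.0225 = 173 evaluable, or 173/0.8 ≈ 216 randomized. Power is 44% at n = 72 and 52% at n = 90. A one-sided test still needs 136 evaluable, 170 randomized.
- 25 percentage points, 60% to 35%: (1.384 + 0.575)² / 0.0625 = 61.4. With continuity correction, 61.4/4 × [1 + √(1 + 4/(61.4 × 0.25))]² = 69.2, so 69-70 evaluable and 87-88 with drop-out. This is close to 90.
- 25-point drops from 65% or 70% give 85-87 with drop-out on the same basis.
- Relative 25% from 82% (to 61.5%) gives 74.5, or 93 with drop-out; from 84% (to 63%) it gives 68, or 85. Both are without continuity correction.

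So 90 can be approached by several routes, none of them stated.

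**2. Rate ratio 0.75 under the negative binomial model.**
For control mean μ and dispersion k, var(log RR) = [1/μ + 1/(0.75μ) + 2k]/n. Then
n = (1.96 + 0.8416)² / (ln 0.75)² × [bracket] = 7.849/0.08276 × [bracket] = 94.84 × [bracket].

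Limit: with n = 72 the bracket may not exceed 72/94.84 = 0.759. Even at an unlimited fall rate (1/μ = 0) this needs k below 0.38. With all 90, 90/94.84 = 0.949, so k must be below 0.47.

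**3. Values of μ and k consistent with the Background.**
Solve P(0) = (1 + kμ)^(−1/k) and P(1) = P(0)·μ/(1 + kμ). For 60% fallers, half of them repeat: k = 0.453, μ = 1.136. The bracket is 0.880 + 1.174 + 0.906 = 2.960, so n = 94.84 × 2.960 ≈ 281 evaluable, or 351 randomized. At n = 72 the SE is √(2.960/72) = 0.203, and power is Φ(0.2877/0.203 − 1.96) = 29%. At n = 90 it is 35%.

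| Fallers | Repeat among fallers | k | μ | Power, n = 72 to 90 |
|---|---|---|---|---|
| 60% | 50% | 0.45 | 1.14 | 29-35% |
| 60% | 60% | 1.00 | 1.50 | 25-30% |
| 60% | 70% | 1.79 | 2.32 | 21-25% |
| 60% | 80% | 3.15 | 5.36 | 15-18% |
| 65% | 50% | 0.24 | 1.19 | 35-42% |
| 70% | 50% | 0.05 | 1.24 | 41-49% |
| 70% | 60% | 0.44 | 1.59 | 36-43% |
| 75% | 60% | 0.21 | 1.61 | 43-51% |

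(At 75% fallers a repeat share of 50% is below what even a Poisson model gives, so that row is omitted.) Simulation with fitted negative binomial models, 400 runs for each of the 50%, 60% and 70% repeat rows at 60% fallers, gave 19-39% over the two sample sizes.

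**4. Dependence on the model.** For any count distribution with 40% non-fallers, the squared coefficient of variation is at least 0.4/0.6 = 0.667. That caps power for a rate ratio of 0.75 at about 56% (n = 72) or 66% (n = 90). At 70% fallers the cap is 75-84%, so above 60% the conclusion relies on the negative binomial shape.

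**5. Detectable effect, as an illustration.** With k = 0.453, μ = 1.136 and n = 72, 80% power is reached at a rate ratio near 0.54: 2.80 × √((0.880 + 1.618 + 0.906)/72) = 0.61 = −ln 0.54.

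**The case against.** The strongest reply is that the document never gives the fall rate or dispersion used for sizing. They come from two sources that are not shown, and the Background offers only two inequalities from the literature. This stands. The power figures are therefore conditional on assumed inputs and are given as a range. A reader might infer that the document's own data fix power at one low value; they do not.

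Second, falls frequency may mean the proportion of fallers, since the Background calls such a percentage a fall rate and a relative risk of falling is among the planned analyses. Read as 25 percentage points, 90 is essentially recovered. This also stands, and it means that 90 cannot be called a plain arithmetic slip. Nor can a reader infer that the 25-point reading must be its origin, because a relative 25% cut from about 82-84% fallers lands in the same place. But 60% to 35% is a 42% relative reduction (25/60), and the section does not say that fallers were the outcome sized on.

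Third, 72 is pessimistic: people who drop out still contribute follow-up time, and six weeks of monitoring precede the 12 months. Hence the range up to 90. Adding the six weeks (μ × 58/52) moves the 60%/50% case only to 31-38%.

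Two further inferences should not be drawn. The cited group-exercise trial of 130 people, not significant with "IRR 0.68 during intervention; 0.74 during follow-up", does not bound this trial's power, because its analysed numbers, exposure and variability are not given here. The sentence that the size "This sample size will also be sufficient to identify between-group differences in the secondary outcomes" lacks target differences, but that is detail an article may leave to the full protocol.

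**Conclusion.** The concern holds in conditional form. If "25% reduction in falls frequency in the intervention group" means a rate ratio of 0.75 tested by negative binomial regression, 90 per group does not give 80% power. With 60% fallers, power is about 15-35% for 72 to 90 per group; with 60-75% fallers and 50-80% of them repeat fallers, about 15-50%. A relative 25% drop in the proportion of fallers from 60% is also underpowered, needing 173 evaluable per group.

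This rests on a two-sided 5% test, on Background figures standing in for the unseen sizing inputs, and on a negative binomial shape. At exactly 60% fallers the shortfall does not depend on that shape. What is established is that the effect, the outcome and the sample size in this section do not fit together as worded. How 90 was obtained cannot be determined from the document.

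**What to change.** Keep 180 participants and revise Power calculation and sample size:

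1. Name the outcome sized on (fall rate or proportion of fallers), and say whether 25% is relative or in percentage points.
2. Give the baseline, dispersion, test and sidedness taken from the two sizing sources.
3. Restate the power for a 25% relative reduction in fall rate, and the rate ratio detectable with 80% power, under the negative binomial model. Show both as a range over plausible baselines and dispersions. The sponsor should compute these from its own sources rather than adopt the illustrative values above.
4. State that a non-significant result will be interpreted from the confidence interval of the rate ratio, including whether it excludes a 25% reduction.

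The cost is rewording and a less favourable stated power. No extra participants or data collection are needed.
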